### Interim analyses {21b}

A single interim analysis using the same statistical approach as for the final analysis will be performed when half the patients have reached 36 weeks’ PMA. The study will be stopped at this interim if (1) there are persistent biochemical signs of vitamin D toxicity (hypercalcemia Ca level >11 mg/dl, ionized Ca >1.55 nMol/l with phosphorus >4 mg/dl, and 25-OH-vitamin D level >150 ng/ml) that are otherwise unexplained and are seen in multiple infants or (2) there is a >95% probability that extra vitamin D increases by more than 15% (i.e., risk ratio >1.15) the rates of death or individual major morbidities unlikely to be related to vitamin D supplementation, specifically BPD, hospital-acquired infections, necrotizing enterocolitis, or spontaneous intestinal perforation by themselves or as a composite outcome with death. Because of the importance of the outcomes at 2 years CA, enrollment will be stopped for benefit at interim analysis only if there is a ≥98% probability that vitamin D reduces the ordinal respiratory support outcome at 36 weeks’ PMA.

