### Composition of the data monitoring committee, its role and reporting structure {21a}

The data monitoring committee will comprise two independent members with expertise in neonatal research: [name], MD, and [name] [name], MD. Additionally, a qualified statistician, [name], will be included to provide statistical expertise. They will review the interim analysis results when half the patients have reached 36 weeks’ PMA.

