### Adverse event reporting and harms {22}

The research team perform daily monitor for any adverse event related to excessive vitamin D intake. If hypercalcemia (serum calcium >10.5 mg/dl or ionized Ca >1.55 mmol/l) is present, other laboratory parameters, such as phosphorus or magnesium, will be considered. It is common in this population to have high calcium levels with low phosphorus while in parenteral nutrition due to unadjusted calcium/phosphorus ratios. If that is the case, we will recommend modifications to the clinical team and monitor closely. If hypercalcemia occurs and other causes (e.g., low phosphorus) cannot be excluded, the NICU medical director will be contacted to determine if signs of vitamin D toxicity are found (nephrocalcinosis, trismus, feeding intolerance), stop the study drug, and notify the parents and IRB.

Due to the high mortality in the more immature infants in the study (22–25 weeks), only if unexpected or inexplicable death happens will it be communicated immediately to the IRB. If not, twice a year, a report of severe adverse events (deaths) will be shared with the IRB as part of the follow-up evaluation to allow the study to continue.

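### The interim toxicity stopping rule prints its ionized-calcium limit in nanomoles instead of millimoles per litre, a factor of 10^6 too low

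*Protocol article*

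**What the plan says.** In the protocol article, Interim analyses {21b} sets one interim look, when half the patients have reached 36 weeks' postmenstrual age. Stopping rule (1) concerns toxicity and lists these laboratory signs: "hypercalcemia Ca level >11 mg/dl, ionized Ca >1.55 nMol/l with phosphorus >4 mg/dl, and 25-OH-vitamin D level >150 ng/ml". The signs must persist, and the rule adds the qualifier "that are otherwise unexplained and are seen in multiple infants".

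Adverse event reporting and harms {22} uses an ionized-calcium limit with the same number for daily monitoring of individual infants: "If hypercalcemia (serum calcium >10.5 mg/dl or ionized Ca >1.55 mmol/l) is present". No other section gives an ionized-calcium limit.

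The data monitoring committee section {21a} assigns the interim results to a committee of two members with neonatal research expertise and a statistician: "They will review the interim analysis results when half the patients have reached 36 weeks".

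**The concern.** The two sections give the same analyte and the same number with different units: nMol/l in {21b} and mmol/l in {22}. They cannot both be right. The one that looks wrong is the threshold on which the trial could be stopped for harm.

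A nanomolar limit does not discriminate, because every infant with a measurable ionized calcium exceeds it. How much of the rule is then lost depends on how the parenthesis is read, since neither an 'and' nor an 'or' joins the total-calcium and ionized-calcium limits. A stopping threshold should be usable as printed, without a second section to decode it.

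**Working it through.** **Inputs**

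- Ionized-calcium limit in {21b}: "ionized Ca >1.55 nMol/l with phosphorus >4 mg/dl", that is 1.55 × 10^-9 mol/l as printed.
- Ionized-calcium limit in {22}: 1.55 mmol/l, that is 1.55 × 10^-3 mol/l.
- Total-calcium limit in {21b}: "hypercalcemia Ca level >11 mg/dl".
- Molar mass of calcium: 40.08 g/mol. This is a physical constant and is not given in the article.

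**Step 1: ratio of the two ionized limits**

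(1.55 × 10^-3) / (1.55 × 10^-9) = 10^6.

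**Step 2: both limits in mg/dl**

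mg/dl = mmol/l × 40.08 / 10.

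- {22}: 1.55 × 40.08 / 10 = 6.2 mg/dl.
- {21b} as printed: 1.55 × 10^-6 × 40.08 / 10 = 0.0000062 mg/dl.

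**Step 3: which unit was meant**

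The total-calcium limit in the same parenthesis converts to 11 × 10 / 40.08 = 2.74 mmol/l. An ionized limit of 1.55 mmol/l is on that scale; 1.55 nmol/l is about six orders of magnitude below it. So {21b} points to mmol/l by itself, and {22} confirms it.

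**Step 4: what the rule still screens as printed**

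| Reading of the parenthesis | Laboratory conditions | Always met by an infant with an ionized reading | Still screening |
|---|---|---|---|
| Either calcium limit is enough (the connector used in {22}) | 3: calcium, phosphorus, 25-OH-vitamin D | calcium | 2 of 3 |
| All items required together | 4: total calcium, ionized calcium, phosphorus, 25-OH-vitamin D | ionized calcium | 3 of 4 |

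Under the first reading, an infant with phosphorus >4 mg/dl and 25-OH-vitamin D >150 ng/ml would satisfy the numerical limits with a normal calcium. Under the second, total calcium still has to exceed 11 mg/dl and only the ionized criterion is lost. These counts show which conditions still work, not how restrictive each one is.

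**The case against.** The strongest reply is that this is an obvious misprint without consequence. Its parts are as follows.

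- **The slip corrects itself.** The number is the same in both sections, {22} prints the right unit, and a neonatal expert on the committee would recognise a millimolar analyte. This is probably true. It bears on how serious the error is, but does not make the printed limit correct.
- **The remaining conditions carry the rule.** The 25-OH-vitamin D limit is very selective. With the assumptions in Sample size {14} (mean 25 ng/ml, SD 12, true increase 33%), the expected intervention mean is 25 × 1.33 = 33.25 ng/ml. If the SD is the same in that arm, 150 ng/ml lies (150 − 33.25) / 12 = 9.7 SD above it. The signs must also meet the persistence and multiple-infant qualifiers. This stands, and no scenario in the article shows the misprint changing a stopping decision.
- **The wording requires hypercalcemia.** The parenthesis opens with that word, so an infant with normal calcium hardly fits it whatever unit follows, and a reader who borrows the connector from {22} would find the right unit there too. This makes the worse of the two readings less likely, but it does not restore the ionized criterion under either one.
- **Protection is not weakened.** A limit that is too low makes the rule easier to meet, never harder, and individual infants are monitored daily against the correct unit in {22}. This also stands: the risk runs towards counting an infant wrongly, not towards missing toxicity.
- **The operative protocol may be right.** The article condenses a fuller document that is not shown. The finding therefore applies to the printed text only.

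The difference between the total-calcium limits (11 mg/dl in {21b}, 10.5 mg/dl in {22}) is not part of this point, since the two can serve different purposes: stopping the trial and monitoring one infant.

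**Conclusion.** The concern holds as a minor point. The ionized-calcium limit in stopping rule (1) is printed 10^6 times too low, and as written that criterion screens out nobody. The conclusion rests on the two printed units and a unit conversion; the only outside figure is the molar mass of calcium, and the ratio does not depend on it.

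The likely effect on conduct is small, for the reasons conceded above, and nothing in the sample size, power or efficacy analysis depends on this limit. It deserves correction because it is a decision threshold in a safety stopping rule for extremely preterm infants, and it contradicts another section of the same article.

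**What to change.** In Interim analyses {21b}, replace the unit so that the limit reads ionized Ca >1.55 mmol/l, as in {22}. Check that the full protocol and any document the monitoring committee works from carry the same unit.

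While that line is open, stating whether total and ionized calcium are joined by 'and' or 'or' would remove the double reading; the unit correction does not depend on it.

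The unit correction costs one edit. No analysis, sample size or other threshold changes.

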### Criteria for discontinuing or modifying allocated interventions {11b}

Two independent blinded-to-treatment group investigators review the electronic medical records of the study infants daily during their admission to the NICU. The study drug will be discontinued if vitamin D toxicity is suspected, at the attending physician’s discretion, and for the period the infant is not receiving feeding during the intervention period.

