### Participant timeline {13}

Screening for infants meeting inclusion criteria is performed daily. The infant enrolled in the study will be randomized between 24 and 96 h after birth.

The first sample of blood is obtained soon after consent is obtained. The intervention will be stopped 28 days after birth; a second blood sample is collected with the next usual laboratory test after finishing the intervention (around 1 month postnatal), and the third sample at 36 weeks or before discharge, whichever occurs first.

The study intervention (placebo vs. extra vitamin D) is given if the infant is feeding within the first 28 days after birth and the vitamin D intake, relevant laboratory results, respiratory support, and growth parameters are obtained from the medical records during the NICU stay and during a 2-year follow-up appointment.

Standard follow-up assessments [26] will be conducted at 22–26 months’ adjusted age, including neurologic examination and neurodevelopmental and behavioral assessment. Additionally, we will collect data on long-term respiratory outcomes, including recurrent wheezing (modified International Study of Asthma and Allergies in Childhood questionnaire [27]) and respiratory infections, to evaluate early childhood pulmonary health (Fig. 1).

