## Data collection and management

### Plans for assessment and collection of outcomes {18a}

The study data are largely obtained from the patients’ electronic medical record by the research team. Automatic data checks identify values outside the expected range at data entry to prompt verification that the data are correct.

Head circumference (assessed using tape) and length (assessed using a length board) are measured by research team members trained to achieve highly reliable measurements at 1 month and 36 weeks’ PMA.

Neurodevelopmental assessment, including BSID-IV at 22–26 months corrected age, Gross Motor Function Classification System, and hearing and vision evaluation, will be performed by certified examiners by the National Institute of Child Health and Human Development Neonatal Research Network [29]. Moderate or severe NDI is defined as a composite of neurologic, developmental, hearing, and vision status. Using the BSID-IV, a moderate delay in the cognitive domain is defined as 70–84, severe delay < 70, and profound delay ≤ 54. Other assessments include a Gross Motor Function Classification Score of ≥2, hearing impairment as bilateral permanent hearing loss that hinders the child’s ability to comprehend examiner directions, with or without amplification, and vision impairment characterized by bilateral acuity less than 20–200 with amplification.

Additionally, we will collect data on long-term respiratory outcomes, including recurrent wheezing (modified International Study of Asthma and Allergies in Childhood questionnaire [27]) and respiratory infections, to evaluate early childhood pulmonary health.

Vitamin D metabolite determination: A total maximum blood volume of <1 ml is obtained for the entire study duration (3 samples of 0.3 ml of whole blood), with daily clinical labs. Specimens are placed in a gold-top microtainer, stored in the research refrigerator until separation of serum in the next 6 h, and frozen at −80 F before shipping in batches for analysis to King’s University College in Ontario, Canada.

Vitamin D metabolites are extracted using liquid-liquid extraction (LLE) and immunoextraction [30, 31] and subjected to liquid chromatography-tandem mass spectrometry analysis using Waters ACQUITY UPLC/Xevo TQ-S instruments. The focus will be on abundant vitamin D metabolites, including 25-OH-D_3_, 25-OH-D_2_, and 3-epi-25-OH-D_3_.

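### Interim toxicity criterion (1) needs a vitamin D level that is not scheduled when toxicity is suspected, so it can read as not met after study drug was stopped in several infants

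*Protocol article*

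**What the plan says.** All places are in the Protocol article.

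- **The criterion.** Interim analyses {21b} would stop the trial on persistent biochemical signs. The calcium part reads "hypercalcemia Ca level >11 mg/dl, ionized Ca >1.55 nMol/l with phosphorus >4 mg/dl". The list then continues to the vitamin D level, with further conditions: "phosphorus >4 mg/dl, and 25-OH-vitamin D level >150 ng/ml) that are otherwise unexplained and are seen in multiple infants". It is applied once, with the timing set by postmenstrual age: "A single interim analysis using the same statistical approach as for the final analysis will be performed when half the patients have reached 36 weeks’".
- **The samples.** Participant timeline {13} schedules three. For the first, "The first sample of blood is obtained soon after consent is obtained". Then "a second blood sample is collected with the next usual laboratory test after finishing the intervention", and a third at 36 weeks or before discharge. Section {18a} confirms three samples of 0.3 ml, frozen "before shipping in batches for analysis" at an outside laboratory.
- **Stopping in the individual infant.** Section {11b}: "The study drug will be discontinued if vitamin D toxicity is suspected". Section {17b} likewise stops drug or placebo on concern about toxicity, without unblinding the NICU staff and research team. Section {22} starts its work-up at total calcium >10.5 mg/dl or ionized calcium >1.55 mmol/l. At that point "other laboratory parameters, such as phosphorus or magnesium, will be considered", and study drug can be stopped after the NICU medical director is contacted.

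**The concern.** Criterion (1) is the only trial-level stopping rule aimed at vitamin D toxicity. Criterion (2) concerns death and morbidities that the protocol itself regards as unlikely to be related to the supplement.

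The rule depends on a level that the schedule does not supply when an infant is suspected of toxicity. The individual safety pathway also works against the rule. Stopping the drug promptly makes it less likely that the signs persist, and less likely that the post-treatment sample still exceeds 150 ng/ml. The more careful the bedside monitoring, the harder the trial-level criterion is to meet.

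The data monitoring committee's stated role ({21a}) is to review the interim results, and it is not among those whom {17b} and {22} name for notification of suspected toxicity. It could be told that criterion (1) is not met without learning that drug had been stopped in several infants.

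**Working it through.** **1. The plan's own figure on this scale.** Sample size {14} gives a routine mean of 25 and SD of 12 ng/ml, a 33% increase, and 37 infants per group for ≥90% power at >95% posterior probability. With a flat prior this corresponds to a one-sided 5% test. The difference is 0.33 × 25 = 8.25, and n = 2 × (1.645 + 1.282)² × 12² / 8.25² ≈ 36.2, so 37 per group, with power 0.905. The figure reproduces and is not in dispute. Criterion (1) has no stated operating characteristics.

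**2. Where 150 ng/ml lies.** From the planned routine mean: (150 − 25)/12 = 10.4 SD. From the planned intervention mean: (150 − 33.25)/12 = 9.7 SD. Only a gross outlier meets the level component.

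**3. The sections side by side.**

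| Item | Criterion (1), {21b} | Individual pathway and schedule |
|---|---|---|
| Total calcium | >11 mg/dl | >10.5 mg/dl ({22}) |
| Ionized calcium | >1.55, printed in nMol/l | >1.55 mmol/l ({22}) |
| Total and ionized joined by | a comma in a list closed by 'and' | 'or' ({22}) |
| Vitamin D level | >150 ng/ml required | none scheduled between baseline and end of treatment ({13}, {18a}) |
| Course of the signs | must persist | drug can be stopped on suspicion ({11b}, {17b}, {22}) |

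An infant whose total calcium meets criterion (1) has already passed the lower cut-off that opens the work-up in {22}.

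**4. How far a level could fall before the second sample.** The protocol gives no kinetics, so everything in this step is assumption: first-order decline, half-life 7 to 28 days, and no further intake after the stop. Level needed at the stop = 150 × 2^(gap / half-life).

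- Gap 7 days: 150 × 2^(7/28) = 178, up to 150 × 2^(7/7) = 300 ng/ml.
- Gap 14 days: 150 × 2^(14/28) = 212, up to 150 × 2^(14/7) = 600 ng/ml.

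Next, let the stop day be uniform over days 10 to 28, the second sample uniform over days 28 to 35, and the level at the stop uniform over the range shown. The simulated chance that an infant above 150 ng/ml at the stop is still above it at the second sample is:

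| Half-life | 150–200 | 150–250 | 150–300 ng/ml |
|---|---|---|---|
| 7 days | 1% | 4% | 8% |
| 14 days | 5% | 15% | 26% |
| 21 days | 11% | 30% | 47% |
| 28 days | 18% | 44% | 63% |

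It is below 50% in 11 of 12 scenarios. Taking 'multiple' as at least two, the chance that two or more exceed 150 ranges from <1% to 68% with three truly toxic infants, and from <1% to 93% with five.

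If the last dose is on day 28, the per-infant chance is 22% to 72% for levels of 150–200 ng/ml and 56% to 91% for 150–300 ng/ml.

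Two omissions pull in opposite directions. Intake that continues after the stop (fortified feeds in Table 1, and the routine supplement allowed by {11d}) would slow the fall. The calcium, phosphorus and persistence conditions would lower the chance of meeting the whole criterion.

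**The case against.** A fair defence has five parts.

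- **Silence is not absence.** The timeline lists research samples. Phosphorus and magnesium in {22} are examples, and {11d} bars extra venipuncture for the study, not a level ordered clinically. A condensed article may leave the work-up to the full protocol. This stands: one can say that no level is scheduled, not that none is taken.
- **Confirmation is defensible.** Section {22} notes that high calcium with low phosphorus is common on parenteral nutrition. A rule that halts a trial may reasonably require confirmed, unexplained toxicity in several infants. This stands as a reason to ask for a level, but it does not help if the level comes only after the drug has been withdrawn.
- **The wording is loose.** Read strictly, {21b} would require both total and ionized calcium, whereas {22} needs either. The conjunctive reading of the vitamin D level is the natural one, but the ambiguity is real and is itself something to settle.
- **Batching is no proven obstacle.** By the interim look the second and third samples are due for infants who have reached 36 weeks, and nothing says they will not be assayed in time. This stands; equally, nothing says they will be.
- **Other oversight exists.** Section {11b} has records reviewed daily, and {17b} and {22} send suspected toxicity to the medical director and the IRB, with {17b} adding the statistician. This stands.

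A reader might infer that a true toxicity signal is unlikely to meet criterion (1). The protocol does not support that as a conclusion, because the answer turns on half-life, peak and stop day, none of which it gives. Infants who become hypercalcemic late or complete the course may still show a high second sample. A reader might also infer that the aim of not worsening other outcomes rests on this check. Objectives {7} ties that aim to named secondary outcomes, none of which depends on criterion (1).

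**Conclusion.** The concern holds as a conflict between sections that the article itself fixes: the sampling times, the action on suspicion and the interim rule. No vitamin D level is scheduled when toxicity is suspected, and early stopping works against both the persistence and the level that criterion (1) requires. The criterion can therefore read as not met although study drug was stopped in several infants for suspected toxicity.

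That it can happen follows from the text alone, on the natural reading that all listed signs are required. How often is not established: 1% to 63% per infant for the level component is a range under stated assumptions, not an estimate for this trial. The gap concerns the interim criterion and what the data monitoring committee sees, not safety oversight as a whole. It should be corrected, because the rule addresses the specific known harm of the higher-dose arm and the correction is cheap.

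**What to change.** Reconcile {11b}, {13}, {17b}, {18a}, {21b} and {22} so that criterion (1) can be judged on data the trial will have for infants whose drug was stopped early. In the same revision:

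- Settle the total calcium cut-offs (>11 versus >10.5 mg/dl), the ionized calcium units (nMol/l versus mmol/l), and whether total and ionized calcium are joined by 'and' or 'or'. Which values and clinical rules apply is for the investigators.
- State that the scheduled samples of the infants in the interim analysis will be assayed before the look.
- Give the data monitoring committee the count, by arm, of infants whose study drug was stopped for suspected toxicity, whether or not criterion (1) is met. The statistician already knows the allocation ({17a}), so clinical and research staff need not be unblinded.

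The cost is a short amendment, one batch shipment timed to the interim look, and one added table in the interim report. These steps need no blood beyond the three planned samples (3 × 0.3 = 0.9 ml).

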### Methods for additional analyses (e.g., subgroup analyses) {20b}

Subgroup analyses of both RR/odds ratio and risk difference will be performed to assess effect modification by BW, gestational age, sex, race, infants who receive at least 80% of the possible doses (infants with minimal time when feedings were discontinued) and baseline 25-OH-D_3_ level (each assessed in one variable at a time analyses) and of different risk strata (assessed using multiple variables). Bayesian hierarchical models with interaction terms between the treatment group indicator and the prespecified potential modifiers will be used. The conservative Bayesian approach of Dixon and Simon [34] will be applied as it allows for a priori specification of how likely (or unlikely) it is for subgroup differences to be present, and to shrink the subgroup estimates to the overall mean treatment effect. The prior distributions for main effects will be the same for subgroup analyses as for the primary endpoint analysis. A Normal(0, SD = 0.7) will be used for interaction terms. Point estimates of treatment effect and 95% CrI for each subgroup will be reported along with probability of benefit using a forest plot.

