### Relevant concomitant care permitted or prohibited during the trial {11d}

No more than 400 IU/day of vitamin D enteral supplementation as part of routine care is allowed in any group during the first 28 days after birth. The infant will only receive the study drug (extra vitamin D or placebo) if receiving feedings. The blood collection for enrolled infants is only collected with usual laboratory testing, and no additional venipuncture for the study will occur.

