### Methods in analysis to handle protocol non-adherence and any statistical methods to handle missing data {20c}

Per-protocol analyses will be conducted for the primary and major secondary outcomes using the same methods as for the interim analyses. The per-protocol analysis dataset will include all infants who received the randomized intervention (routine care or intervention).

If missing data occurs, it will be assumed to be noninformative (missing at random), and it will be imputed under a Bayesian framework by simulating from the posterior predictive distribution.

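### Receipt of at least 80% of doses is analysed as an effect modifier, but it is determined after randomization and allocation could affect it, so that subgroup's treatment effect is not protected by randomization

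*Protocol article*

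**What the plan says.** The subgroup section ({20b}) names birth weight, gestational age, sex, race and baseline 25-OH-D3 as potential effect modifiers. In the same list it puts "infants who receive at least 80% of the possible doses (infants with minimal time when feedings were discontinued". All are handled alike: "Bayesian hierarchical models with interaction terms between the treatment group indicator and the prespecified potential modifiers will be used", and "Point estimates of treatment effect and 95% CrI for each subgroup will be reported along with probability of benefit using a forest plot". Nothing sets the dose-receipt row apart from the baseline rows.

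Three other sections determine who falls in that row:

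- Concomitant care {11d}: "The infant will only receive the study drug (extra vitamin D or placebo) if receiving feedings".
- Discontinuation {11b}: "The study drug will be discontinued if vitamin D toxicity is suspected". It is also withheld "for the period the infant is not receiving feeding during the intervention period".
- Adverse events {22}: after hypercalcemia for which other causes cannot be excluded, the medical director is contacted to determine whether "signs of vitamin D toxicity are found (nephrocalcinosis, trismus, feeding intolerance".

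For the per-protocol analysis, section {20c} states: "The per-protocol analysis dataset will include all infants who received the randomized intervention (routine care or intervention". It is planned for the primary and major secondary outcomes. The main analysis is by intention to treat ({20a}).

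**The concern.** A subgroup analysis is a randomized comparison when membership is fixed before treatment starts. Dose receipt is not fixed then. It accumulates over the first 28 days and depends on whether the infant is fed and whether the product is stopped for suspected toxicity. The article itself lists feeding intolerance among the toxicity signs, so it allows a route from allocation to membership. Matching the products in appearance does not close that route.

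If allocation changes which infants reach 80%, the two arms of the subgroup contain different kinds of infant. The forest plot would then show a probability of benefit that partly measures selection. It would stand beside rows that are properly randomized, with nothing to warn the reader. The row is also likely to attract attention, because it looks like the effect in infants who actually received the treatment.

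**Working it through.** **The plan's own figures.** The article gives no figure for this analysis. Its primary sample size does not depend on the point and reproduces: 33% of 25 is 8.25 ng/ml, and with SD 12, one-sided 0.05 and 90% power, 2 × (1.645 + 1.282)² × 12² / 8.25² = 36.2, so 37 per group and 74 in total.

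**Is membership a baseline variable?** No. By {11d} and {11b} it follows feeding and toxicity stops after randomization. By {22} feeding intolerance is a possible drug effect. The other named modifiers are patient characteristics or a baseline level.

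**How large could the bias be with no true effect?** All inputs here are assumptions, because the article gives no rates of dose receipt or outcome by feeding course.

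- Each arm has 5% never dosed, 25% poor feeders and 70% good feeders.
- All good feeders reach 80% of doses, no never-dosed infant does, and 60% of control poor feeders do. The control subgroup is therefore 0.70 + 0.25 × 0.60 = 85% of the arm.
- Risk of grade 2 BPD or worse, including death, is 0.354 in good feeders (0.2565 + 0.0475 + 0.05) and 0.7375 in poor feeders (0.3375 + 0.15 + 0.25), the same in both arms.

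Subgroup risk = (0.70 × 0.354 + p × 0.7375) / (0.70 + p), where p is the share of the arm made up of poor feeders who reach 80%. In the control arm p = 0.15, so the risk is 0.4217 and the odds 0.7291.

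| Change in active-arm membership | p | Active risk | Active odds | Spurious OR |
|---|---|---|---|---|
| +10 points | 0.25 | 0.4549 | 0.8346 | 1.14 |
| +5 points | 0.20 | 0.4392 | 0.7832 | 1.07 |
| none | 0.15 | 0.4217 | 0.7291 | 1.00 |
| −5 points | 0.10 | 0.4019 | 0.6721 | 0.92 |
| −10 points | 0.05 | 0.3796 | 0.6118 | 0.84 |
| −15 points | 0 | 0.3540 | 0.5480 | 0.75 |

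A simulation of the full five-level ordinal outcome on the same inputs (90 per arm, 6,000 replicates, proportional-odds score estimate, Normal prior with mean 0 and variance 0.70 on the log OR) gave ORs of 1.00, 0.93, 0.83 and 0.75 for losses of 0, 5, 10 and 15 points. The share of null trials with a posterior probability of benefit above 80%, the threshold in Sample size {14}, was 19%, 26%, 39% and 51%.

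These runs estimate the effect within the subgroup. They do not fit the interaction model of {20b} with its Normal(0, SD = 0.7) prior. That prior would pull the displayed estimate toward the overall effect. It reduces the distortion but does not correct for selection.

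**Per-protocol set.** If the wording in {20c} is taken to keep every control infant and drop never-dosed active infants, the same simulation (80% mortality assumed among the never-dosed) gives a null OR of 0.94 at 3% never dosed and 0.80 at 10%. The 80% threshold is crossed in 26% and 48% of trials. With the same exclusion in both arms the OR is 1.00 and about 19% to 20% cross.

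**The case against.** The strongest reply on the subgroup is that both arms get a blinded, volume-matched product under the same feeding rule, so dose receipt may well be independent of allocation. The Discussion also judges 800 IU/day unlikely to cause toxicity. This stands as a limit: with no effect of allocation on dose receipt or survival, the table gives an OR of 1.00. It does not rescue the row as a baseline modifier, because the interaction would then contrast infants with smooth and interrupted feeding, who differ in prognosis as well as dose. The direction is also open: better tolerance of the active product would push the OR above 1.

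Three stronger readings are tempting, and the article does not support them.

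- A reader might infer that the per-protocol set excludes infants from the active arm only. That follows only from a literal reading of the parenthesis in {20c}. The participant timeline {13} and concealment {16b} describe the intervention as placebo versus vitamin D, and Table 1 lists placebo under routine care up to day 28, so a symmetric meaning is available. If receiving routine care meant receiving the 400 IU/day supplement, which starts only at about 120 ml/kg/day, controls could be the ones lost. The wording is ambiguous; one-arm exclusion is not established.
- A reader might infer that infants who die early cannot reach 80%. The plan speaks of possible doses without defining the denominator. Counted up to death, an infant fed until then could reach 100%.
- A reader might infer that the trial's conclusions are at risk. The primary and secondary outcomes are analysed by intention to treat, and neither analysis discussed here feeds a stopping rule.

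**Conclusion.** The point holds for the dose-receipt subgroup. It is a post-randomization variable placed among baseline modifiers, and its between-arm contrast is not protected by randomization. Bias arises only if allocation changes dose receipt or survival, and it can run either way. On assumed inputs with no true effect, losing 5 to 15 percentage points of poor feeders from the active subgroup gives an OR of about 0.93 to 0.75, before any shrinkage from the planned interaction prior. The article gives no rates from which the actual size could be judged, so these figures are illustrations and not predictions.

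The per-protocol wording is a secondary point: it should be clarified, and it has not been shown to be asymmetric. Both analyses are supplementary.

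**What to change.** 1. In {20b}, remove receipt of at least 80% of possible doses from the effect-modification list and from the forest plot. If the interest is in infants likely to tolerate feeding, use a predictor of feeding tolerance measured at or before randomization.
2. If the effect of doses actually received is wanted, specify it as a separate exploratory complier or principal-stratum analysis. State its assumptions and define possible doses, including how death within the 28 days is counted.
3. In {20c}, define the per-protocol set by one criterion for both arms: at least one dose of blinded study product, placebo or vitamin D.

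Items 1 and 3 are mainly changes of wording. Item 2 is real work: it introduces a new estimand with untestable assumptions and lower precision in about 180 infants, and it can be left out without loss to the main analysis. Sample size and trial conduct do not change.
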